### Study intervention

#### Usual care versus psychosocial intervention

Patients in the control and the intervention group will all receive usual care, which may include dialysis treatment, medication and a nutritional regimen. The scope of usual psychosocial care will be assessed at each participating centre. To prevent co-intervention bias, patients participating in other studies or treatments aimed at reducing fatigue will be excluded. Patients will not be restricted in any activities. Any significant changes in health status and/or treatment will be monitored throughout the study.

Patients assigned to the intervention group will receive face to face psychosocial counselling directed to reducing and managing fatigue. Patients will be involved in 4–6 individual protocolled counselling sessions (45 min each) over a period of 16 weeks, and will perform several practical (home) assignments/exercises. The sessions will be given by a local social worker who is already employed at the participating dialysis centre.

#### Intervention protocol

The intervention protocol has been developed by the VUmc research team, of which one of the members works as a health psychologist [name]. The protocol is partly based on pre-existing interventions that have already been proven effective in the treatment of fatigue in other patient groups [45–47]. Previous research into the perpetuating factors of (chronic) fatigue in patients with chronic diseases in general [18, 19] and kidney diseases in particular [12, 17] also provided valuable input for protocol development, as well as a (yet unpublished) qualitative interview study on the subjective experience of fatigue in ESRD patients. This qualitative study was initiated by the VUmc research team, and was conducted prior to protocol development.

The protocol consists of eight modules, addressing various behavioural, psychological, cognitive and social aspects that influence fatigue. These factors encompass sleep-wake rhythm and sleep hygiene routines, physical activity, energy distribution, dysfunctional cognitions with respect to fatigue, social support (communication, needs and boundaries), catastrophizing thoughts and worrying. Additional file 1 gives an extended overview of the content of the intervention modules.

#### Intervention instruction for social workers

All involved social workers will be visited by a member of the VUmc research team for instruction on how to use the protocol. Prior to the instruction visit, a digital version of the intervention protocol will be provided. The instruction involves a brief explanation of the eight modules, the method of module selection, counselling procedures and the use of registration forms. Social workers will also be informed about background, main aims and study procedures. All participating professionals are experienced in working with intervention protocols and psychosocial counselling. During the study, a member of the research team will be available to answer questions about the protocol and counselling procedures.

#### Intervention procedures

Because of the variability in influencing factors of fatigue in ESRD patients, counselling will be customised to each patient individually. A certain procedure will, however, be followed. After the patient has returned the baseline measurement (see data collection), the social worker will be informed by the research team and commissioned to start the intervention. The social worker will invite the patient to an intake session in which they jointly will assess and decide which modules are most appropriate. A decision aid is provided in the intervention protocol. A maximum of three to four modules will be selected, which will be addressed in 4–6 individual counselling sessions of about 45 min each. Each module will include one or more (take-home) exercise(s). The patient and social worker agree on the timing and location of the subsequent counselling sessions and whether a partner or relative will participate in (a selection) of the sessions.

### Data collection and management

This study will follow a mixed method design in which both quantitative and qualitative data will be collected.

#### Quantitative measurements

To determine the effects of the intervention on the short- and long-term, repeated quantitative measurements will be conducted (four survey measurements over a period of 13 months). These surveys will be completed by the participants in both the intervention and control groups.

The primary outcome will be fatigue severity, measured by a subscale of the CIS-fatigue [43]. The secondary outcome will be quality of life (kidney disease specific), as measured by the KDQOL [48]. Questionnaires on coping style, illness cognitions/perceptions, catastrophizing thoughts, depression, social support and overall perceptions of mastery and control will be included since these outcomes may be potential moderating or mediating factors. In addition, various medical parameters and demographics will be studied as potential modifiers. All outcome measures and assessment instruments are listed in Table 1.

**Table 1 Tab1:** Measures and instrumentation

	Instrumentation	T0	T1	T2	T3
Primary outcome measures					
Fatigue severity	Checklist Individual Strength (CIS-fatigue) [43]	x	x	x	x
Secondary outcome measures					
Quality of life	Kidney Disease and Quality of Life Short Form (KDQOL-SF) [48]	x	x	x	x
Mediating/moderating variables					
Social support	Social Support Inventory (SSL-I + SSL-D) [58] + subscale Utrechtse Coping Lijst (UCL) [59]	x	x	x	x
Illness cognitions	Illness Cognition Questionnaire (ICQ) [60]	x	x	x	x
Illness perceptions	Illness Perception Questionnaire (IPQ-R) [61]: subscale emotional representation	x	x	x	x
Coping	Cognitive Emotion Regulation Questionnaire (CERQ) [62]	x	x	x	x
Catastrophizing thoughts	Fatigue Catastrophizing Scale (J-FCS) [63, 64]	x	x	x	x
Mastery	Mastery Scale [65]	x	x	x	x
Depression	Patient Health Questionnaire: Depression (PHQ-9) [66]	x	x		
General effect modifiers					
Demographic variables	Self-report: age, gender, education, ethnicity, social status, employment	x			
Medical history and comorbidity	Self-report: treatment, treatment frequency, transplantability	x			
Medical parameters	Medical records: sleep medication, Epo, Hb, Urea, Creatinine, Protein, Albumin, CRP, weight, height	x			x

For each individual in the intervention group, measurements will be obtained prior to the start of the study period (T0 - baseline), immediately after the intervention period of 16 weeks (T1 - post- treatment), three months after the intervention period (T2 – short-term follow-up) and nine months after the intervention period (T3 – long-term follow-up). For patients participating in the control group, measurements will be obtained according to the same time frame (baseline; + 16 weeks; + three months; + six months). (Participants will be able to decide themselves how and when they fill out the questionnaires (online/paper-pencil; at the dialysis centre/at home). The overall duration of the study will be 13 months for each participant (in both intervention and control group).

#### Qualitative process and effect evaluation

Besides quantitatively measuring intervention effects, understanding the determinants of intervention success or failure, and insight into the nature of the intervention delivery is essential [37, 49–51]. Therefore, we will perform a qualitative evaluation of both the process and perceived effects parallel to/following the effectiveness RCT [52].

##### Interviews and focus groups

Individual interviews and focus groups will be conducted to gain insight into patients’ and social workers’ expectations of, and experiences with the intervention.

Approximately 15 patients who are assigned to the intervention group will be invited for a semi-structured interview about attitudes and expectations regarding the intervention (prior to the start of the intervention). After the post-intervention measurement (T1), again, a subset of 15 (different) patients will be invited for an interview to assess their experiences with the intervention. Several additional topics will be explored such as the nature of the relationship with the (medical) social worker, (changed) attitudes regarding fatigue and future health/fatigue expectations. Purposeful, maximum variation selection will be applied in order to explore attitudes from a broad range of participants (taking into account variation in demographics, treatment and treatment history).

Interviews will take 60–90 min and will take place at a time and location that best suits the patients. In addition, 10 patients will be invited to a focus group discussion to share experiences, validate and deepen issues generated from the interviews, and discuss suggestions to improve the protocol. The duration of this focus group will depend on the capacity of the participating patients, but will not exceed 2.5 h (including breaks).

All participating social workers will be interviewed about their expectations regarding the utility and effectiveness of the intervention protocol. After finishing the last intervention session with the last participating patient, they will be interviewed about their experiences and asked to evaluate the intervention protocol. The semi-structured interviews will take place at the dialysis centre or by phone, and will take approximately 30 min. After the study period, 8–10 (medical) social workers will be invited to a two-hour focus group in order to exchange experiences, deepen issues derived from the interviews and discuss potential improvements of the protocol.

Both interviews and focus groups will be guided by a pre-defined topic list, which will be discussed within the VUmc research team and members of the advisory group in advance. After approval of participants, all interviews and focus groups will be audio-taped and transcribed verbatim. Written interview reports will be sent back to interview and focus group participants to validate findings and improve credibility [53, 54].

Gained insights from both interviews and focus groups will be used to improve the intervention protocol and treatment feasibility, and to determine facilitators and barriers to the successful engagement of both patients and professionals.

##### Implementation fidelity

To assess the implementation fidelity of the intervention, all social workers will be asked to audio-tape one of the counselling sessions held with the second or third patient to whom they offer the intervention. In order to collect a variety in recorded sessions they will be asked to record the second or third session, under the pre-condition that patients provide written informed consent for audio-tapings. The research executive will collect all audio-tapings and assess whether the modules are offered according to the protocol guidelines and face to face instruction by using a pre-constructed observation checklist.

All social workers will also be asked to provide general information about the dialysis population at their centre and the total number of patients who are eligible, decline and agree to participate. Social workers will be asked to provide registrations for each participating patient on the number and duration of counselling sessions, the involvement of partners or relatives, drop-out rates and reasons for drop-out. Registration forms will be provided prior to the beginning of the trial.

##### Data management and privacy procedures

All privacy sensitive data (any information relating to an identified or identifiable natural person) will be handled according to the rules of protecting personal data (Personal Data Protection Act/Wet Bescherming Persoonsgegevens). All identifying information of participants will be coded and de-personalised. Data will be stored in a secured project file on the VUmc network. Access to the study data will be restricted to involved research members, who all signed a privacy statement.

Signed informed consent forms and returned coded/anonymized questionnaires will be stored in a locker separately from study records that link to participant identifying codes. Only the first responsible researcher [name] has access to these documents. Data entry will be performed by a research assistant. Data integrity will be assured by random consistency checks/re-entry of data. Audio taped records of interviews/focus groups will be removed after transcripts are provided. Archived electronic data will be kept for a maximum of ten years, informed consent forms for a maximum of five years, in line with the policy guidelines of the Quality Committee of the EMGO+ institute (http://www.emgo.nl/kc/). Collected data will be processed anonymously in publications and reports, preventing identification of individual participants.

### Data analysis

Descriptive statistics for outcome measures will be presented. A paired *t*-test will be used to investigate statistical significant differences in the effects (primary and secondary outcomes) between intervention and control groups. Statistical significance will be defined as *p* ≤ 0.05. Statistical analyses will be performed using the SPSS system for Windows, version 22.0. A detailed analysis plan will be developed in collaboration with a statistical expert. This plan will also address the analysis of potential effect modifiers and confounders, and further exploratory analyses.

Qualitative data will be subjected to a thematic analysis [55, 56]. Themes recurring from the data (interview and focus group transcripts) will be categorised and coded. The research team will meet on a regular basis and discuss emerging themes throughout the research process. Preliminary findings will be discussed with the members of the advisory group.

The quantitative outcomes will be related to, and integrated with the qualitative findings to determine correspondence and discrepancies in perceived and measured effects. The advisory group will be actively involved in discussing findings and final conclusions.

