
Non-pharmalogical interventions targeted at behavioural, psychological, cognitive and social factors, may potentially be successful in decreasing fatigue in dialysis patients. Studies on fatigue in patients with cancer [23–28], chronic pain [29], chronic fatigue syndrome [30, 31], brain injury [32] and muscular diseases [33, 34], suggest that such psychological or psychosocial interventions are effective in reducing fatigue that is caused by multiple interacting factors. As far as we know, the literature does not describe (evidence-based) psychological or psychosocial interventions to reduce fatigue in ESRD patients. This can be seen as a deficiency, since such interventions may, based on other populations and causes of fatigue, also be effective in reducing the experienced fatigue of patients on dialysis.

The primary objective of this study is to investigate the efficacy of a psychosocial intervention on the reduction of fatigue provided to patients on dialysis treatment, compared to dialysis patients receiving usual care. Secondary objectives are to study the efficacy of the intervention on improving the QoL and to investigate the possible mediating and moderating effects of coping style, illness cognitions and perceptions, catastrophizing thoughts, feelings of depression, feelings of control and mastery, and social support. A randomised controlled trial (RCT) will be conducted to achieve these objectives. Next to the RCT, a process evaluation will be conducted to gain an in-depth understanding of both patients’ and professionals’ expectations of, and experiences with the psychosocial intervention and its implementation. In addition, the degree to which the intervention is implemented as intended (implementation fidelity) will be evaluated [35–37].

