## Methods/Design

### Design and setting

This study follows a mixed method design in which both quantitative and qualitative methods will be applied for data collection. The study involves a two-arm, multi-centre RCT involving patients with ESRD undergoing a dialysis treatment (either haemodialysis or peritoneal dialysis). Patients will be randomly assigned to either the intervention group (usual treatment and psychosocial counselling by a social worker in the dialysis department, aimed at reducing fatigue) or the control group (usual treatment). Intervention efficacy will be quantitatively measured (repeated measures/self-report questionnaires/medical records) (Fig. 1). A qualitative process evaluation will be conducted to gain insight into patients’ and professionals’ perspectives on outcomes and implementation procedures. Both interviews and focus groups will be applied for data collection. The study will be conducted at both academic and non-academic dialysis centres in the Netherlands. The aim is to include a maximum of 10 centres in total.

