#### Sample size

The sample size calculation will be based on examining the difference between the psychosocial intervention versus usual care on the primary outcome ‘subjective experience of fatigue’ (four repeated measurements) [43]. Thirty-seven patients will be needed in each condition, assuming a significance of 5 % (two-tailed) and power of 80 % in detecting a clinically relevant change of eight points on the primary outcome variable [25, 44]. We expect a drop-out rate of 30 % based on an unpublished study by Dialysis Centre Groningen in 2011 (14 % mortality, 5 % kidney transplantation, 11 % remaining).

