### Randomisation

Patients who meet the trial criteria and give informed consent to participate in the study will be assigned to either the intervention or the control group. Patients in the control group will receive usual treatment. Patients in the intervention group will receive a protocolled psychosocial intervention provided by a social worker. Computer-generated block randomisation will be performed, ensuring the equal (1:1) allocation of patients to either the intervention or control group at each participating centre. To ensure concealment, the block sizes will not be disclosed. The allocation procedure is performed by an independent research colleague who is not involved in the study. The researcher [name] will inform patients about the allocation outcome and subsequent study procedures. For ethical reasons, and if desired, patients allocated to the control group will be offered the opportunity to participate in the intervention group after the third measurement. Due to the nature of the intervention neither participants nor social workers can be blinded to allocation. Data entry will be performed by a research assistant who is not informed about group allocation.

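### The primary test named is a paired t-test, but the two randomised arms are independent, so the test does not match the comparison it is meant to make

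*Protocol article*

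**What the plan says.** All references are to the protocol article.

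- **Data analysis** names one inferential method for the quantitative outcomes: "A paired *t*-test will be used to investigate statistical significant differences in the effects (primary and secondary outcomes) between intervention and control groups". It sets significance at p ≤ 0.05 and SPSS 22 as the software. It also announces a detailed analysis plan, to be written with a statistical expert, that will additionally cover modifiers, confounders and exploratory work.
- **Design and setting** describes a parallel trial: "The study involves a two-arm, multi-centre RCT involving patients with ESRD undergoing a dialysis treatment", with individual allocation: "Patients will be randomly assigned to either the intervention group".
- **Randomisation** gives the mechanism: "Computer-generated block randomisation will be performed, ensuring the equal (1:1) allocation of patients to either the intervention or control group at each participating centre".
- **Background** states the primary objective as the efficacy of the intervention on fatigue "compared to dialysis patients receiving usual care".
- **Sample size** rests on "examining the difference between the psychosocial intervention versus usual care on the primary outcome". It asks for 37 per arm, and the error rate, power and target difference behind that number are given as "assuming a significance of 5 % (two-tailed) and power of 80 % in detecting a clinically relevant change of eight points".

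No matching of patients across arms is described anywhere.

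**The concern.** A paired t-test needs a one-to-one link between the two sets of observations. Blocks within centre balance the numbers per arm but do not link any intervention patient to a particular control patient. The test can therefore be run in only two ways. It can be applied to pre/post values inside each arm, which tests change from baseline. Or unrelated patients can be paired across arms, which has no basis in the design.

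The first route is the natural use of the test and the harmful one. Within-arm change combines any intervention effect with natural course, attention and regression to the mean. Shared change is plausible here: patients must score at least 35 on CIS-fatigue to enter, the outcome is self-reported, and participants are not blinded. A significant fall in the intervention arm beside a non-significant fall in the control arm is easily read as efficacy, although the arms have never been compared. The same test is named for the secondary outcomes, so the defect reaches quality of life as well.

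**Working it through.** **1. Test against design.** The objective and the sample size both concern intervention versus usual care. The arms are independent samples of individually randomised patients. The paired test requires linked observations. These statements are incompatible whatever numbers are used.

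**2. The plan's own figure.** The article gives 37 per arm, 8 points, two-sided 5% and 80% power, but no SD. The 37 can therefore be back-solved but not confirmed. With the two-sample formula, SD = 8 × √(37/2) / (1.960 + 0.842) = 12.28. Using the t distribution it is 12.12. If 37 is the number enrolled and about 26 remain after 30% drop-out (37 × 0.7 = 25.9), the implied SD is 10.30 (normal) or 10.10 (t). The article does not say which reading applies.

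**3. What within-arm paired tests do when the intervention has no effect.**

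Inputs:
- SD 12.1, implied by step 2 if 37 are evaluable.
- Pre/post correlation 0.5, assumed.
- SD of change = 12.1 × √(2 × (1 − 0.5)) = 12.1.
- A mean improvement m common to both arms, assumed and varied.

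For n per arm, the test statistic is noncentral t with n − 1 degrees of freedom and noncentrality m√n / 12.1. For example, n = 37 and m = 4 gives 4 × 6.083 / 12.1 = 2.01. Let p be the chance that one arm's test is significant. The chance that the intervention arm is significant and the control arm is not is then p(1 − p), which cannot exceed 25%.

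| Shared improvement m | n = 37: intervention arm significant | n = 37: intervention significant, control not | n = 26: intervention arm significant | n = 26: intervention significant, control not |
|---|---|---|---|---|
| 0 | 5% | 2.4%* | 5% | 2.4%* |
| 2 | 16% | 14% | 13% | 11% |
| 3 | 31% | 21% | 23% | 18% |
| 4 | 50% | 25% | 37% | 23% |
| 6 | 83% | 14% | 68% | 22% |
| 8 | 97% | 2.5% | 90% | 9% |

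*Counts only significant improvement in the intervention arm: 0.025 × 0.95 = 2.4%. Counting either direction gives 0.05 × 0.95 = 4.75%.

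The n = 26 columns keep SD 12.1. With the SD of 10.1 implied by the other reading of the sample size, the n = 26 results nearly equal the n = 37 columns (m = 3: 31% and 21%; m = 4: 49% and 25%).

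**4. Sensitivity.** Simulation of 20,000 trials per setting, with SD of change 8 to 12 and shared change 2 to 6 points, gave these ranges:
- 37 per arm: intervention arm significant in 17–99%, misleading pattern in 0.7–25%.
- 26 per arm: 13–96% and 4–25%.

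An independent-groups t-test on the same change scores rejected in 4.7–5.3% of trials in every setting, including those with no shared change.

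**5. Arbitrary pairing across arms.** With SD 12.1, the noncentrality is 8 / (12.1 × √(2/37)) = 2.84 for 37 pairs. Power is 79% on 36 degrees of freedom, against 80% on 72 for the independent test. For 26 pairs the noncentrality is 2.38, and power is 63% against 65%. Simulated type I error under such pairing was 4.8%. This route costs little power, but the choice of pairs is arbitrary and unequal drop-out would leave patients without a partner.

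**The case against.** The strongest reply is that the sentence itself asks for a comparison between groups, so the word paired may be a slip for an independent t-test, perhaps on change scores. Nowhere does the article say that efficacy would be inferred from significance in one arm and not the other. That is fair: the error rates in step 3 apply only if the test is run within arms. It does not rescue the sentence, because a reader cannot carry out the named test on the stated comparison.

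A second reply is that a detailed plan is promised. What an article leaves to that plan is not a fault, but here the article commits to a specific test, and the announcement neither withdraws nor qualifies it. If the later plan names another test, it will depart from the published protocol on the primary analysis.

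Third, the size of the problem depends on assumptions. Shared shifts of 3 to 4 points lie near the 25% ceiling at 37 per arm, and neither the shift nor the correlation comes from the article. This stands, and the full range should be quoted.

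Fourth, arbitrary cross-arm pairing would keep the type I error near 5%, so a paired test is not bound to be invalid in every conceivable use. This also stands, but nothing in the design supports such pairing.

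**Conclusion.** The concern holds. The test named for the primary and secondary outcomes contradicts the parallel, unmatched design and the between-arm objective. That conclusion rests on the text alone.

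The size of the harm is conditional on a within-arm reading, no true effect, a change SD of about 12.1 and equal shared change in both arms. At 37 per arm the misleading one-arm pattern then occurs in about 2% to 25% of trials over shared changes of 0 to 8 points, with 21–25% at 3 to 4 points. Because the defect concerns the primary test, it must be corrected before the analysis.

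**What to change.** Replace the sentence in Data analysis with a between-arm comparison, for example: The primary analysis estimates the mean difference in CIS-fatigue (intervention minus control), with a 95% confidence interval, from a linear model with allocated arm and baseline CIS-fatigue as terms, in all randomised patients according to allocation. KDQOL-SF is analysed in the same way. Changes within each arm are described but not tested.

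The essential part is the independent-groups comparison. Baseline adjustment (ANCOVA) is the recommended form because the score is already collected at T0; an unpaired test on change scores would also hold its error rate. The sentence becomes fully executable once the analysis plan names the measurement time it applies to, given four measurements and the offer of the intervention to controls after the third.

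The cost is one sentence in the protocol or analysis plan. It needs no new data, SPSS 22 can fit the model, and the change of test does not itself alter the sample size: 37 per arm agrees with a two-sample calculation at an SD of about 12.3 if all 37 are evaluable.

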**Methods/Design:**

This study follows a mixed-methods design in which both quantitative and qualitative data will be collected. A multi-centre, randomised controlled trial (RCT) with repeated measures will be conducted to quantitatively assess the efficacy of the psychosocial intervention in reducing fatigue and improving QoL in ESRD patients. Additional secondary outcomes and medical parameters will be assessed. Outcomes will be compared to patients receiving usual care. A sample of 74 severely fatigued dialysis patients will be recruited from 10 dialysis centres. Patients will be randomly assigned to the intervention or control group. Outcomes will be assessed at baseline, post intervention/16 weeks, and at three and six-month follow-ups. A qualitative process evaluation will be conducted parallel to/following the effectiveness RCT. Interviews and focus groups will be conducted to gain insight into patients’ and social workers’ perspectives on outcomes and implementation procedures. Implementation fidelity will be assessed by audio-taped and written registrations. Participatory methods ensure the continuous input of experiential knowledge, improving the quality of study procedures and the applicability of outcomes.

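### When the paired t-test is corrected, a plain t-test in its place would still use baseline fatigue at best by differencing, omit centre and not use the follow-up visits jointly

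*Protocol article*

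**What the plan says.** The Data analysis section of the protocol article gives a paired t-test as its only inferential method, to investigate "differences in the effects (primary and secondary outcomes) between intervention and control groups". It names no time point, baseline term or centre term. It then announces a detailed plan, to be written with a statistical expert, that will also deal with effect modifiers, confounders and exploratory analyses.

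Three other parts of the article bear on that choice:

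- **Baseline.** Patient recruitment places randomisation after the baseline measurement, and Table 1 lists CIS-fatigue at T0, T1, T2 and T3.
- **Centre.** Randomisation: "Computer-generated block randomisation will be performed, ensuring the equal (1:1) allocation of patients to either the intervention or control group at each participating centre". The Discussion relies on this balance against differences between social workers.
- **Repeated measurements.** Sample size describes the primary outcome with the words "four repeated measurements" and concludes "Thirty-seven patients will be needed in each condition", for a "clinically relevant change of eight points on the primary outcome variable" at two-sided 5% and 80% power, with 30% drop-out expected.

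Randomisation also says that control patients may be offered the intervention after the third measurement, which is T2.

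**The concern.** The named test does not fit the question. A paired t-test needs pairs, and there are none across two independent arms. Run on before-and-after scores, it tests change within an arm and gives no randomised contrast. That is a fault of validity and comes first.

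The point here is what remains if the only correction is to replace paired by unpaired. The test would then be valid, but:

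- it could use T0 only by subtracting it, which is less efficient than adjusting for it unless the correlation is very high;
- it would have no term for centre, so its standard error would ignore the blocking;
- it would look at one visit or one difference at a time, which does not match a sample size that refers to four measurements, and it would drop patients who lack the visit being tested.

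The abstract plans a total of 74 patients, so precision is scarce. All the variables needed to improve it are already collected.

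**Working it through.** **Inputs from the article.** Difference 8 points; two-sided 5%; power 80%; 37 per arm (74 = 2 × 37); expected drop-out 30%, so 37 × 0.7 = 25.9, taken as 26 per arm.

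**Inputs assumed.** The article gives neither an SD nor a correlation.

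- SD: back-solved below, under two readings of 37.
- Correlation ρ between baseline and follow-up CIS-fatigue: 0.3 to 0.7. Entry requires a score of at least 35, which narrows the baseline range and may lower ρ, so the low end should not be dismissed.
- Centre intraclass correlation (ICC): 0.02 to 0.10.

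**1. The plan's own figure.** Without an SD, 37 can only be back-solved. Power is taken from the noncentral t distribution with non-centrality 8 / (SD × √(2/n)).

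- If 37 per arm are analysed, 80% power implies SD 12.1: 8 / (12.1 × √(2/37)) = 2.84. The normal approximation gives 12.3.
- If 37 already allows for the loss and 26 per arm are analysed, 80% power implies SD of about 10.1.

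**2. Variance of each analysis at one visit, relative to the raw follow-up score.**

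- Raw-score t-test: 1
- Change-score t-test: 2(1 − ρ)
- ANCOVA on baseline: 1 − ρ²

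The SD is multiplied by the square root of the factor. At ρ = 0.5, ANCOVA gives 12.1 × √0.75 = 10.5.

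**3. Power for 8 points.**

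| ρ | ANCOVA factor | Change factor | ANCOVA, 37/arm, SD 12.1 | ANCOVA, 26/arm, SD 12.1 | Change score, 26/arm, SD 12.1 | ANCOVA, 26/arm, SD 10.1 |
|---|---|---|---|---|---|---|
| 0.3 | 0.91 | 1.4 | 84% | 69% | 51% | 84% |
| 0.4 | 0.84 | 1.2 | 86% | 72% | 57% | 86% |
| 0.5 | 0.75 | 1.0 | 90% | 77% | 65% | 90% |
| 0.6 | 0.64 | 0.8 | 94% | 83% | 74% | 94% |
| 0.7 | 0.51 | 0.6 | 98% | 91% | 86% | 98% |

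The raw-score t-test has 80% at 37 per arm and 65% at 26 per arm with SD 12.1, and 80% at 26 per arm with SD 10.1. ANCOVA is ahead of both t-tests at every ρ examined. Its lead over the change score shrinks as ρ rises.

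**4. Centre.** With 1:1 blocking within centre, the unadjusted standard error includes between-centre variance that does not affect the contrast. Removing it multiplies the variance by about 1 − ICC, that is 0.98 to 0.90. At 37 per arm and SD 12.1, power moves from 80% to about 81% (ICC 0.02) or 84% (ICC 0.10).

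**5. Repeated visits.** In a mixed model with arm-by-visit and baseline-by-visit terms and an unstructured covariance, complete data give the same T1 contrast as ANCOVA at T1. T2 then helps only where data are missing. The larger gain would come from averaging T1 and T2: the factor (1 + ρ)/2 − ρ² is 0.56 at ρ = 0.3 and 0.44 at ρ = 0.6, giving 88% and 94% at 26 per arm with SD 12.1. That is a different contrast and assumes the same 8-point effect at both visits.

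**6. What the four measurements did in the sizing.** The article does not say. If 37 came from averaging three follow-up visits, the single-visit SD would be 12.1 / √((1 + 2ρ)/3), that is 16.6 at ρ = 0.3 and 13.5 at ρ = 0.7. A one-visit t-test would then have about 54% to 71%. If 37 came from a plain two-group formula, a one-visit t-test keeps the planned 80%. The documents do not settle which.

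**The case against.** The strongest reply is that the article defers a detailed analysis plan, and that covariates, centre terms and the handling of repeated visits commonly belong there. That stands as far as it goes: the lack of covariate detail is no finding by itself, and the plan, which is not shown, may already correct the test. But the article states a test, and it describes the plan as additionally covering modifiers, confounders and exploratory work, not as replacing that test.

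A second reply is that once the invalid test is replaced, the choice of model belongs to the same edit. That is right, and the fix is worded accordingly.

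Three stronger readings are tempting, and the documents do not support them:

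- **That the baseline is ignored.** A before-and-after paired test uses T0 by differencing. What it lacks is adjustment within a between-arm comparison.
- **That the trial loses power its sample size already counted on.** This cannot be shown, because the SD, the correlation and the role of the four measurements are not given.
- **That power at T1 is 65%.** This charges the whole 30% loss by week 16, although the article gives no period for it and participation lasts 13 months. It also assumes that 37 makes no allowance for loss, which the article does not say.

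Nor is there a figure for patients seen at T2 but not at T1. Of the expected 30% loss, 14 percentage points are deaths, which cannot produce that pattern.

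**Conclusion.** The point holds as a free improvement to a stated method. The named paired test has to be replaced in any case. A plain unpaired t-test would be valid, but less efficient than a comparison adjusted for baseline and centre, and no closer to the repeated-measurement basis cited for the sample size.

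Under the assumed SDs and ρ of 0.3 to 0.6, baseline adjustment adds about 4 to 14 percentage points of power over a raw-score test at 37 per arm (SD 12.1), the same at 26 per arm if 26 was the intended analysed number (SD 10.1), and 4 to 18 points at 26 per arm with SD 12.1. Over a change-score test at 26 per arm and SD 12.1, it adds 18 points at ρ = 0.3, 9 at 0.6 and 5 at 0.7. The direction does not depend on these assumptions within the range examined; the size does. Centre adds little, and leaving it out errs towards too large a standard error. T2 strengthens a T1 contrast only through missing data.

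**What to change.** In the same edit that removes the paired t-test, state as primary analysis a between-arm comparison of CIS-fatigue adjusted for baseline CIS-fatigue and centre. Either form serves:

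- ANCOVA at one named time point; or
- a linear mixed model of T1 and T2 with arm, visit, arm-by-visit, baseline, baseline-by-visit and centre, including all randomised patients with at least one follow-up, and with the visit that carries the primary contrast named in advance. With at most 10 centres and 74 / 10 = 7.4 patients per centre on average, a random intercept for centre is reasonable.

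Leave T3 out of the primary contrast, because control patients may have received the intervention by then. Use the same model for KDQOL-SF. State the SD and correlation behind 37 per arm, how the four measurements entered the calculation, and whether 37 allows for the 30% loss.

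The cost is wording in the analysis plan. No data are added, and SPSS, the package the article names, fits the model.
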